### Part 2: Follow-Up of the Use of Screening Methods

A total of 6 months after a positive test result, the DKFZ contacts the respective participants in arms A and B to request permission for obtaining the reports of any subsequently conducted colonoscopies. Separate information sheets and consent forms are being used and the name of the treating gastroenterologist is requested. Relevant information from colonoscopy reports are being extracted and entered into an electronic database by two independent, trained data extractors and checked for inconsistencies.

Claims data of screening colonoscopies and FITs conducted within 1 year after the initial invitation or information letter is being provided by AOK BW in an aggregated manner per study arm (ie, A, B, and C) and gender. Individual pseudonymized claims data regarding the usage of FITs and colonoscopies is available for participants in the intervention arms upon specific informed consent.

In addition, results of screening colonoscopies in the age group of 50-54 years is being documented by the gastroenterologists in standardized survey forms, which are mandatory for billing. The billing company *MEDIVERBUND AG* captures the data electronically, anonymizes it, and sends it to the DKFZ for the analysis. Assignment to the initial study arms—A, B, or C—is possible only after consent.

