### Objectives

The primary outcome that will be investigated is as follows: determine the proportion of people completing a FIT within 1 year after receiving a personal invitation letter within each trial arm.

Secondary outcomes are to determine the following:

The rate of positive test results.The rate of performing a colonoscopy after a positive test.The rate of performing a colonoscopy after a negative test.The rate of discovered advanced colorectal neoplasia (ie, advanced adenomas and cancer).The positive predictive value of the test.The rate of performing a screening colonoscopy, in general, within 1 year.

Gender-specific analyses will be conducted.

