### Inclusion and Exclusion Criteria

Inclusion criteria for receiving a letter are as follows: (1) aged 50-54 years, (2) enrolled in the AOK Family Doctor Program (HausarztProgramm) of AOK BW (Hausarztzentrierte Versorgung [HZV] contract: § 73b SGB V), and (3) did not receive an invitation in previous rounds of AOK BW model projects in previous years. Exclusion criteria for receiving a letter are as follows: (1) had an insurance-recorded colonoscopy within the past 5 years, (2) had a previous cancer diagnosis, (3) being deceased, and (4) being dependent on care.

Participants with a positive FIT result detected with the provided test kit are contacted by the DKFZ during the second part of the study to follow up on usage and outcome of colonoscopies.

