Insurants randomized to arms A and B, who decide to take the FIT offer, are asked to sign the informed consent form. By signing this, they agree to the FIT analysis; to receive a written test result, which will also be sent to the family physician if not contradicted; to data storage and evaluation (ie, FIT result, age, gender, and first three digits of postal code); and to be recontacted during follow-up in case of a positive result. Optionally, they can allow the DKFZ to receive pseudonymized claims data from CRC screening participation in routine practice within 1 year after the initial invitation.

As proposed by the FIT manufacturer, participants are being instructed to spread the tip of the test stick over the freshly passed whole feces at various points until the tip’s grooves were filled with feces, and then to reinsert the probe into the device. The serrated probe that is attached to the device cap collects 10 mg feces into 2 mL of buffer. The FIT and the informed consent sheet are mailed to the DKFZ in a postpaid envelope. Upon arrival at the DKFZ, the FITs are stored in a fridge and separated from person-identifying information (ie, pseudonymized). The FITs are then sent by cooled transport to an external certified laboratory: Labor Limbach, Heidelberg, Germany, DIN EN ISO 15189 accredited. Trained laboratory personnel blinded to the randomization arm perform the analysis in a fully automated manner using the original OC-Sensor Pledia FIT device. Samples are disposed of after the analysis. As recommended by the manufacturer, the cutoff for a test result to be positive is 50 ng Hb/mL buffer (equal to 10 µg Hb/g feces). Results above the upper analytical limit of 1000 ng Hb/mL buffer are not diluted and not retested. Collection, arrival, and analysis dates of fecal samples are recorded. The DKFZ receives the laboratory reports, each checked and signed by a certified medical doctor. Additionally, the quantitative test results of the FITs are transferred electronically to the DKFZ, using DocNet plus, version 4 (DocNet Systems GmbH), where they are integrated into the study database.

Missing informed consent forms are being requested before any test analysis starts. Participants with failed tests receive a new test kit (eg, due to failed sampling or if the difference between the day of sample taking and arrival at the DKFZ is more than 7 days without cooling, followed by a negative test result).

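### Colonoscopy use after a positive FIT is tied to a 6-month request for report release, so a rate resting on that contact alone is open to outcome-dependent non-response

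*Protocol article*

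**What the plan says.** The Objectives list "The rate of performing a colonoscopy after a positive test" as a secondary outcome, and the Results section of the Abstract counts it among the main secondary end points.

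Three places describe how it is to be observed:

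- Inclusion and Exclusion Criteria: participants whose study kit is positive "are contacted by the DKFZ during the second part of the study to follow up on usage and outcome of colonoscopies".
- Table 1: the row on colonoscopy use after a positive FIT has the requesting of reports as its only activity, at T2 (6 months after the positive result). Claims-based use of screening stands in a separate block at T3 (1 year), headed as routine practice.
- Part 2 of the Methods: at 6 months "the DKFZ contacts the respective participants in arms A and B to request permission for obtaining the reports of any subsequently conducted colonoscopies". It adds: "Separate information sheets and consent forms are being used and the name of the treating gastroenterologist is requested".

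A second source exists. On the form signed with the kit, participants agree "to be recontacted during follow-up in case of a positive result". The same form offers a further choice: "Optionally, they can allow the DKFZ to receive pseudonymized claims data from CRC screening participation in routine practice". Part 1 has missing forms chased before any test is analysed. Part 2 describes the resulting individual claims as covering use of FITs and colonoscopies in the intervention arms. The other claims feed is aggregated by arm and gender and cannot be linked to a FIT result.

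**The concern.** The 6-month contact asks for release of a report and for a gastroenterologist's name. Someone who had a colonoscopy can supply both. Someone who had none can supply neither, and may have less reason to answer. Whether a person is observed may therefore depend on the event being counted. A responders-only rate is then distorted. Counting non-responders as having had no colonoscopy is a different error, and it lowers the rate whenever anyone who had a colonoscopy fails to reply.

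At stake is the figure that shows whether a mailed FIT leads to work-up. If it rests on the contact alone, readers cannot separate uptake of colonoscopy from willingness to reply.

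**Working it through.** **The plan's own figures.** The article states no expected value for this end point, for FIT positivity or for reply to the 6-month contact. The figures it does state concern FIT use. They reproduce but do not bear on this point. For A vs C with 5844 per arm, the standard error of the log ratio is √(0.65/(5844×0.35) + 0.90/(5844×0.10)) = 0.0431, which gives 3.50 (3.22 to 3.81), as printed.

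**Formulae.** Let T be the true proportion with a colonoscopy among FIT-positives, r1 the reply probability of those who had one, and r0 that of those who had none.

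- Responders only: T·r1 / (T·r1 + (1−T)·r0). This equals T only if r1 = r0 (for T strictly between 0 and 1).
- Non-responders counted as none: T·r1. This is below T whenever r1 < 1, whatever r0 is.
- Non-responders counted as yes: T·r1 + [1 − T·r1 − (1−T)·r0].

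**Illustration** (T, r1 and r0 are all assumptions): T = 0.60, r1 = 0.75, r0 = 0.35.

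- Replies: 0.60×0.75 = 0.45 with and 0.40×0.35 = 0.14 without a colonoscopy, together 0.59.
- Responders only: 0.45/0.59 = 76%.
- Non-responders as none: 45%.
- Non-responders as yes: 0.45 + 0.41 = 86%.

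**Sensitivity to the assumptions**

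| T | r1 | r0 | Responders only | Non-responders = none |
|---|---|---|---|---|
| 0.60 | 0.80 | 0.80 | 60% | 48% |
| 0.60 | 0.80 | 0.60 | 67% | 48% |
| 0.60 | 0.80 | 0.40 | 75% | 48% |
| 0.60 | 0.60 | 0.80 | 53% | 36% |
| 0.70 | 0.80 | 0.80 | 70% | 56% |
| 0.70 | 0.80 | 0.60 | 76% | 56% |
| 0.70 | 0.80 | 0.40 | 82% | 56% |
| 0.70 | 0.60 | 0.80 | 64% | 42% |

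Equal reply gives no bias among responders. If those without a colonoscopy reply more readily, the sign reverses.

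**Scale.** Expected FIT use (35% in A, 17.5% in B) gives 5844×(0.35+0.175) = 3068 users. This is an upper bound for study kits because it includes routine FITs. At an assumed positivity of 5% to 10%, that is about 153 to 307 FIT-positive persons. Were all of them observed, the 95% half-width around 60% would be 1.96×√(0.24/153) = 7.8 points down to 1.96×√(0.24/307) = 5.5 points. The 16-point gap in the illustration (76% against 60%) would exceed that.

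**What the claims add.** The width of the all-yes to all-no bounds equals the share of persons seen by neither source. With the contact alone it is 0.41 in the illustration. If a share c gave claims consent, independently of reply, it becomes 0.41×(1−c). The claims window runs 1 year from the invitation, so it covers at least 6 months after any result issued within 6 months of the invitation (12 − 6 = 6), and less for later results.

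**The case against.** The strongest objection is that the article never says the contact is the only source and never commits to an estimator. It says FIT-positives are contacted to follow up on use, and it provides elsewhere for individual claims on colonoscopy use. The choice of source, denominator and handling of non-response could sit in a full protocol or SAP that is not shown. This stands as far as the estimator goes: silence there is no fault. It does not dispose of the point, because Inclusion and Exclusion Criteria and Table 1 positively assign colonoscopy use after a positive FIT to the report request and list claims separately under routine practice.

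Second, differential reply is inferred. Recontact was agreed beforehand, all FIT-positives in arms A and B are approached, and nothing prevents an answer that no colonoscopy was done. The gastroenterologist's name can hardly be asked for before a colonoscopy is arranged. All of this stands. A reader might infer that the reported rate is biased, and biased upward. The documents do not support that, because they give no reply rates and the table above shows zero and reversed bias under other inputs.

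Third, a reader might conclude that claims should simply replace the contact. The documents do not support that either. The consent is optional and may select people more inclined to have a colonoscopy. It is worded around screening participation, so capture of colonoscopies done to work up a positive FIT is uncertain. The window also starts at the invitation and not at the result.

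**Conclusion.** The point holds as a vulnerability of the stated ascertainment route, not as a demonstrated bias. The separate consent is sought after the colonoscopy decision, and those without a colonoscopy have nothing to release, so reply may depend on the outcome. Size and direction are not fixed by the documents. The 76% and 45% for a true 60% rest entirely on the assumed 60%, 75% and 35%. They show that the effect could matter, not what it is.

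The individual claims consent is given before the result. It may be selective, but it cannot be a response to whether a colonoscopy later took place, which makes it a useful complement. Secondary outcomes are described as descriptive and exploratory, and the primary end point, its tests and its power are untouched. This is a cheap improvement to a named secondary end point, and it can still be made after data collection because it mainly concerns how existing sources are used.

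**What to change.** In Inclusion and Exclusion Criteria, Part 2 and Table 1:

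1. Keep all study-kit FIT-positives in arms A and B as the denominator.
2. Determine colonoscopy use from the individual claims of those who gave the claims consent with the kit, combined with the 6-month replies, including replies that no colonoscopy was done.
3. Report how many persons are observed by each source, and give bounds with those observed by neither counted as all yes and as all no.
4. Report the rate among claims consenters as a check free of outcome-dependent reply. First confirm that the extract includes colonoscopies done to work up a positive FIT and not only screening codes. State that its window is 1 year from the invitation.
5. Use the released reports for findings and positive predictive value.

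The cost is slightly more analysis, an interval in place of a single figure, and possible selection through the optional claims consent, which should be acknowledged. No new source is needed, provided the extract proves to contain work-up colonoscopies.

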**Figure 1 figure1:**
[figure not shown]
Study design. Total expected fecal immunochemical test (FIT) use per study arm: A=35%, B=17.5%, and C=10%. Participants in arms A and B may receive a FIT as part of the intervention or can additionally request it in routine practice. Participants in arm C (ie, control) can only use the FIT in routine practice. Data on the use of screening methods until 1 year after the initial invitation will be collected. AOK BW: AOK Baden-Wuerttemberg; A1 and A2: subgroups of arm A; and B1 and B2: subgroups of arm B.

**Table 1 table1:** Overview of study assessments at relevant time points.

Assessments		T0 (0 wk)	T1								T2 (6 months after positive FIT^a^)	T3 (1 year)
			2 wk	4 wk	6 wk	8 wk	10 wk	12 wk	14 wk	>14^b^ wk		

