**Use of colorectal cancer screening in routine practice within 1 year**												
	Use of FITs^f^	–	–	–	–	–	–	–	–	–	–	✓
	Use of colonoscopy^f^	–	–	–	–	–	–	–	–	–	–	✓
	Colonoscopy reports^g^	–	–	–	–	–	–	–	–	–	–	✓

^a^FIT: fecal immunochemical test.

^b^Duration depends on how long insurants are sending back the FITs.

^c^Arm A: invitation + FIT; arm B: invitation + order; and arm C: information only (ie, control).

^d^Not applicable.

^e^Subrandomization in arms A and B: 50% receive reminder.

^f^Aggregated for all arms and additionally pseudonymized for arms A and B where consent was given.

^g^Anonymized for all arms where consent was given.

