In the randomized substudy, the increase in FIT usage due to a reminder letter in comparison to the one-time invitation will be analyzed. The expected FIT usage in arm A is approximately 40% with the reminder compared to 30% without the reminder; the expected FIT usage in arm B is approximately 20% with the reminder compared to 15% without the reminder. The included sample size of the randomized substudy (ie, 2922 per arm) allows for a precise estimation of the impact of sending a reminder. The expected relative FIT use (95% CI) in subgroups A1 and B1 (ie, received a reminder) compared to the respective subcontrol groups A2 and B2 (ie, one-time invitation only) would be 1.33 (1.24-1.43) and 1.33 (1.19-1.49), respectively. The statistical power to detect an effect of the expected order of magnitude is close to 100%: SAS, version 9.4 (SAS Institute) POWER procedure, two-sided Pearson chi-square test with significance level alpha=.025. For the two comparisons (ie, A1 vs A2 and B1 vs B2), multiple testing was adjusted for, according to the Bonferroni-Holm method. For the most stringent adjustment with alpha=.025 (ie, baseline alpha=.05 with two tests) there is still excellent power.

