### Statistical Analysis

The statistical analysis of this confirmatory study primarily involves comparing the use of FITs in the intervention arms and the control arm within 1 year after the initial letter. In addition, within the intervention arms, the effect of a one-time invitation will be compared to an invitation with a reminder letter.

Comparisons will be done by two-sided chi-square tests for differences in the participation rates. Secondary outcomes will be addressed by descriptive and exploratory analyses. Data for the primary outcome analysis are expected to be complete, as complete information on FITs conducted in routine practice is obtained through insurance claims data (ie, billing codes for laboratory analysis of the FIT), and complete information on FITs conducted through the special offers is directly available from the study center.

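### Routine-practice FIT use is to be supplied by arm and gender only, so the reminder comparisons can be made on study-kit use but not on the total FIT use they appear to be planned on

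*Protocol article*

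**What the plan says.** **Supply of routine data.** Under Part 2: Follow-Up of the Use of Screening Methods, claims for FITs and screening colonoscopies within 1 year are "provided by AOK BW in an aggregated manner per study arm (ie, A, B, and C) and gender". The next sentence adds a second source: "Individual pseudonymized claims data regarding the usage of FITs and colonoscopies is available for participants in the intervention arms upon specific informed consent". Footnote f of Table 1 describes the same two sources: "Aggregated for all arms and additionally pseudonymized for arms A and B where consent was given".

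**Who can consent.** Part 1: Personal Invitation for Colorectal Cancer Screening limits the consent request to kit takers: "Insurants randomized to arms A and B, who decide to take the FIT offer, are asked to sign the informed consent form". Claims access is a further choice on that form: "Optionally, they can allow the DKFZ to receive pseudonymized claims data from CRC screening participation in routine practice within 1 year". In arm B the form goes out only with an ordered kit.

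**Reminder comparison.** Sample Size Calculation states: "The expected FIT usage in arm A is approximately 40% with the reminder compared to 30% without the reminder". For arm B the rates are 20% and 15%. With 2922 people per subgroup it gives ratios of 1.33 (1.24-1.43) and 1.33 (1.19-1.49), power close to 100%, and a Bonferroni-Holm adjustment for the two tests. Statistical Analysis, which calls the study confirmatory, says that "within the intervention arms, the effect of a one-time invitation will be compared to an invitation with a reminder letter".

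**Arm totals.** The legend of Figure 1 gives, in percent, "Total expected fecal immunochemical test (FIT) use per study arm: A=35%, B=17.5%, and C=10", and notes that people in A and B can also obtain a FIT in routine practice.

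**The concern.** The reminder comparison is randomised and multiplicity-controlled, and its planning figures appear to count every FIT, whether from the study kit or a doctor. The stated data flow gives the routine part for whole arms only. The people who matter are those who use a routine FIT and no study kit. They appear in the arm-level count, but nothing assigns them to a reminder subgroup, and they fall largely outside the consented individual data because consent is sought from kit takers.

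Two things are at stake. A reminder may send some people to their doctor for a routine FIT, and a kit-only comparison cannot see this. In addition, the relative effect on kit use is a different quantity from the relative effect on total use, so the published ratio may not be the one that the sample-size section describes.

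**Working it through.** **1. Reproduce the plan's figures.** Inputs from Sample Size Calculation: n = 2922 per subgroup; 40% vs 30%; 20% vs 15%; two-sided alpha 0.025.

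SE(log RR) = sqrt[(1−p1)/(n·p1) + (1−p2)/(n·p2)]; 95% CI = RR × exp(±1.96·SE).

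- A: SE = sqrt(0.6/1168.8 + 0.7/876.6) = 0.0362; RR 1.333 (1.242-1.431).
- B: SE = sqrt(0.8/584.4 + 0.85/438.3) = 0.0575; RR 1.333 (1.191-1.492).

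Power for B: the SE of the difference is 0.00994 under the null (pooled rate 0.175) and 0.00992 under the alternative. Then (0.05 − 2.241 × 0.00994)/0.00992 = 2.79, which is 99.7%. Power for A exceeds 99.99%. All stated figures reproduce.

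**2. Which endpoint do these rates describe?** (40 + 30)/2 = 35 and (20 + 15)/2 = 17.5. These are exactly the arm totals in Figure 1, labelled as total use. Sample Size Calculation also sets 35% and 17.5% against the control arm's 10%, which is routine use. The subgroup rates therefore sit on the total-use scale.

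**3. What can be observed by subgroup?**

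| Component of FIT use | Source | Available by A1, A2, B1, B2? |
|---|---|---|
| Study kit returned | Study centre | Yes |
| Routine FIT, kit taker with optional consent | Individual claims | Yes, but largely people already counted through their kit |
| Routine FIT only, no study kit | Aggregated claims | No: arm and gender only |

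**4. Kit-only comparison.** Let r be the share of each subgroup using a routine FIT and no study kit. The documents do not give r for arms A and B. I assume it equal in both subgroups and let it run from 0 to 10%, the upper end being the control arm's expected rate. The kit-only rate is the planned rate minus r. Routine-only users leave the numerator; the denominator stays 2922.

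| r | A: rates, RR (95% CI) | B: rates, RR (95% CI) |
|---|---|---|
| 0 | 40% vs 30%, 1.33 (1.24-1.43) | 20% vs 15%, 1.33 (1.19-1.49) |
| 5% | 35% vs 25%, 1.40 (1.29-1.52) | 15% vs 10%, 1.50 (1.31-1.72) |
| 10% | 30% vs 20%, 1.50 (1.37-1.64) | 10% vs 5%, 2.00 (1.65-2.42) |

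The differences stay at 10 and 5 percentage points, and power stays at or above 99.7% throughout. If routine use is instead taken as independent of kit use, the kit rate is (total − r)/(1 − r). At r = 10% this is 33.3% vs 22.2% in A and 11.1% vs 5.6% in B: the same ratios, with differences of 11.1 and 5.6 points.

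**5. Total use with unassignable routine users.** Suppose the arm-level number of routine-only users, r × 5844, is known but its split between the two subgroups is not. If all fall in the no-reminder group, the ratio is (p1 − r)/(p2 + r). If all fall in the reminder group, it is (p1 + r)/(p2 − r).

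| r (persons per arm) | A | B |
|---|---|---|
| 1% (58) | 1.26-1.41 | 1.19-1.50 |
| 2.5% (146) | 1.15-1.55 | 1.00-1.80 |
| 5% (292) | 1.00-1.80 | 0.75-2.50 |

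These are extreme allocations, not likely values. They show that arm-level counts cannot stand in for subgroup counts.

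**The case against.** The strongest reply is that no sentence defines the reminder endpoint. The primary outcome is set per trial arm, the completeness statement in Statistical Analysis covers the primary outcome only, and the sample-size text splits use into a part after the first letter and a part after the reminder, which can be read as response to the study's own offer. This stands as far as it goes: the total-use endpoint is an inference. But on the kit-uptake reading the same figures would serve two endpoints, since they also make up the arm totals that include routine practice.

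A second reply is that the insurer randomises and holds the claims, so a subgroup table looks feasible, and a condensed article may leave it to the full protocol. Feasibility is plausible. However, the article does not merely stay silent: it spells out the supply as A, B and C, while using A1, A2, B1 and B2 elsewhere when the subgroups are meant.

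A reader might go further and infer that the reminder comparison cannot be done, lacks power, or rests on wrong figures. The documents do not support this. Kit use by subgroup is available from the study centre, randomisation makes its test valid, power is at least 99.7%, and every stated ratio and interval reproduces.

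Nor should the ratio of 2.00 in arm B be read as an expected result. It needs the full control-arm routine rate to persist, as routine-only use, among people offered a free mailed kit. At r = 5% the B ratio of 1.50 barely passes the stated upper limit of 1.49. The planned chi-square tests compare participation rates, and the differences hardly move.

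**Conclusion.** The point holds as a mismatch between the stated data supply and the apparent endpoint of the reminder substudy. As described, A1 vs A2 and B1 vs B2 can be compared on study-kit use but not on total 1-year FIT use. A kit-only result would be a valid answer to a narrower question: it would be silent on any reminder effect on routine testing, and its ratio could depart from 1.33, up to 1.50 in A and 2.00 in B at the top of the assumed range, with little change in absolute differences.

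This rests on two things that the documents do not state: that the substudy was planned on total use (strongly suggested by the averages and the Figure 1 label), and the size of r, with equal routine-only use in both subgroups. The missing subgroup split does not affect the primary comparison of A, B and C. Severity is moderate.

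**What to change.** Have the insurer tabulate routine FIT use by A1, A2, B1, B2 and C, and by gender. People who also returned a study kit must be identified so that each person counts once; adding claims counts to kit counts would count people with both twice. Then analyse A1 vs A2 and B1 vs B2 on total FIT use, and say so in Statistical Analysis.

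If the split cannot be delivered, state that the substudy endpoint is return of a study-provided FIT within 1 year, and restate the expected rates, ratios and intervals on that basis.

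The first option costs a finer tabulation, with cells smaller than 2922 once split by gender, and a matching step between study-centre and insurer records whose privacy handling must be settled. As the article reports data collection and workup complete in fall 2019, the query may have to be rerun. The second option costs a few sentences and recalculated planning figures, and it gives up any conclusion about the reminder's effect on routine FIT use.
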